**2 JUSTIFICATION**

Internationally, the number of laparoscopic surgeries has been gradually increasing (DANIEL J. RISKIN, MICHAEL T. LONGAKER, MICHAEL GERTNER 2006; KAVIC 1998) and among the anesthetic techniques available, general anesthesia and general anesthesia associated with spinal anesthesia, are among the most used (GERGES et al. 2006; HENNY and HOFLAND 2005).

Due to the physiological changes caused by the pneumoperitoneum (HENNY and HOFLAND 2005; KALMAR et al. 2010) associated with the Trendelenburg position (CLOSHEN et al. 2014; KALMAR et al. 2010), it is speculated the increase in the incidence of delirium in the post -operative of these surgeries.

Thus, due to the lack of published studies on the incidence of delirium, in the postoperative period in laparoscopic oncological surgeries in the Trendelenburg position, it was decided to perform the same.

**3 OBJECTIVES**

The aim of this study was to analyze whether the anesthetic techniques used for laparoscopic oncological surgeries in the Trendelenburg position, differed in relation to the incidence of postoperative delirium.

**MATERIAL AND METHODS**

Prospective, randomized study , including patients from the operating room of AC Camargo Hospital, aged 18 years or older, ASA less than 3, undergoing laparoscopic elective surgery in a Trendelenburg position lasting at least 2 hours in the cephalodeclive and agree to sign the free and informed consent form.

Study will be evaluated by the ethics and research committee (CEP) of the Antônio Prudente Foundation (FAP).

Patients will be sequentially allocated to possible 2 groups. Sequential allocation (FOSSALUZA et al. 2009) will be used to control some confounding variables. Opaque envelopes will be generated and subsequently opened by the operating room anesthesia coordinator prior to surgery that day. The following patients will be excluded:

1. Not wishing to participate in the survey.
2. Absolute contraindications to spinal anesthesia.
3. Difficult airway prediction (possibility of awake intubation.
4. Prior diagnosis of cognitive impairment and / or depression.
5. Chronic use of benzodiazepines (use during last 12 weeks).
6. Referred for postoperative ICU.
7. Anemia (Hemoglobin <10).
8. Current infection.
9. Stage kidney disease> G3a (glomerular filtration rate <45ml / min / 1.73 m2)

10. Body mass index (BMI) characterized by obesity (BMI> 30Kg / m2).
11. History of nausea / vomiting in previous anesthetic procedures.
12. Malignant hyperthermia.

These patients were monitored intraoperatively with cardioscopy, noninvasive pressure, pulse oximetry, capnography, thermometer, bispectral index (BIS) , and neuromuscular blocker monitor.

The patients will be divided into 2 groups: 1) balanced anesthesia + spinal anesthesia with 50 mcg morphine

2) balanced anesthesia + spinal anesthesia with 2.5 ml heavy bupivacaine 0.5% + 50 mcg morphine.

All patients will receive 0.03 mg / kg midazolam intravenous pre-anesthetic medication in the operating room for comfort and 500 ml of crystalloid solution before induction / blockade associated with 4 ml / kg / hour of crystalloid solution plus volume depending on clinical parameters.

Spinal anesthesia will be performed in a sitting position, antisepsis / asepsis with alcoholic chlorhexidine, L3 / L4 space location, 27 G whitacre needle puncture, 0.5 ml shaving and injection lasting 5 to 7 seconds.

Subsequent general anesthesia with pre-oxygenation 8 liters / minute for 5 minutes + fentanyl 3 mcg / kg + propofol 2 mg / kg + rocuronium 0.6 mg / kg will be performed. Anesthesia will be maintained with remifentanil (mcg / kg / min) and desflurane (Fe%).

Hypnosis will be guided by keeping BIS between 40 and 60 and the remifentanil dose will be guided by vital signs.

In both groups, patients will be kept warm with a thermal blanket and their esophageal temperature measured (distance of 40 cm from the incisor teeth) (DANIEI 2008; WANG 2016).

The following parameters will be measured: heart rate, blood pressure, BIS, capnography, saturation, TOF, esophageal temperature and Trendelenburg angle.

The measured moments will be the patient's entry into the operating room, after pre- anesthetic medication, pre-anesthetic induction, after anesthetic induction, after surgical incision, after pneumoperitoneum inflation, after Trendelenburg position, every 15 minutes until the end of the procedure. after extubation.

After the surgical procedure is completed and 5 minutes after extubation, vital signs (blood pressure, heart rate, saturation) will be collected and the patient will be evaluated for delirium. Dipyrone 2 grams and parecoxib 40 mg will be performed with no contraindication for postoperative analgesia.

Afterwards, patients will be referred to the anesthetic recovery room (PACU), where they will continue to be monitored with ECG, noninvasive pressure and pulse oximeters. They will also be evaluated for pain on the numerical rating scale (NRS) (0 = no pain, up to 10 = worst pain), on arrival and every 30 minutes until discharge to the room. Those with NRS> 4 on the PACU will be treated with morphine 1 mg every 10 min or NRS <4. Those with nausea / vomiting will be treated with alizapride 50 mg.

Patients will be assessed for delirium onset using the Confusion Assemenment Method (CAM) (SUPPLEMENT1) in combination with the Richmond Agitation Sedation Scale (RASS) scale (SUPPLEMENT 2).

This evaluation will be performed by nurses, previously trained, upon arrival at the PACU, every 30 minutes until discharge from the post-anesthetic recovery room and every 24 hours until discharge, by the researcher himself. If the patient has an episode of delirium that persists for more than 1 hour, a psychiatrist will be asked for follow-up and treatment.

With regard to statistical analysis, due to the lack of studies involving this specific group of patients, a simulation was carried out with the incidence of delirium seen by Sanders et al 2011.

- Proportion of cases among those exposed: 5%
- Proportion of cases among those not exposed: 21%
- Calculated relative risk: 0.2381
- Significance level: 5%
- Test power: 85%
- Hypothesis testing: single-tailed
- Sample size calculated for each group: 62

Considering losses, the number of patients was stipulated for each group (ANNEX 3).

• Group 1 - “n: 65” - balanced anesthesia + spinal anesthesia with + morphine

50 mcg.

• Group 2 - “n: 65” - balanced anesthesia + spinal anesthesia with 2.5 ml

0.5% heavy bupivacaine + 50 mcg morphine.

Initially, a descriptive analysis of the data will be performed, in which the distribution of absolute / relative frequency will be presented for the qualitative variables and the main summary measures, such as mean, median, maximum, minimum and standard deviation will be presented for the quantitative variables. In order to assess a possible association between the variables of interest and the outcome (delirium and non-delirium), the independence test (chi-square or Fisher's exact) will be applied. In addition, in order to assess and quantify the impact of each independent variable on the outcome of interest, the simple and multiple logistic regression model will be adjusted to the data. In all tests, a significance level of 5% will be set. The analyzes will be performed using SPSS software version 23 and free software R version 3.4

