**3. Disorganized Thinking**

Was the patient's thinking disorganized or inconsistent, with scattered or irrelevant conversion, unclear or illogical flow of ideas, or unpredictable change of subject? (YES) (NO)

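### Nothing in the protocol keeps the people who score delirium unaware of the treatment group

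*Protocol*

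**What the plan says.** The sole objective (section 3, Objectives) is whether the anaesthetic techniques "differed in relation to the incidence of postoperative delirium". The word primary is not used, but delirium is also the basis of the sample size, so it is the primary outcome in substance.

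Material and Methods provides three sets of readings:

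- **Five minutes after extubation:** "the patient will be evaluated for delirium". No rater is named.
- **Recovery room:** "This evaluation will be performed by nurses, previously trained, upon arrival at the PACU", then half-hourly until the patient leaves the PACU.
- **Ward:** "every 24 hours until discharge, by the researcher himself".

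The CAM in Supplement 1 is four yes/no questions answered by the rater. One example is "Was the patient's thinking disorganized or inconsistent".

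On allocation, opaque envelopes are "opened by the operating room anesthesia coordinator prior to surgery that day". The design is described only as prospective and randomized. In the text available, blinding terms occur only in the titles of cited works.

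**The concern.** CAM items on attention, thinking and level of consciousness leave room for borderline answers. A rater who knows the group can resolve those answers differently in the two arms without intending to. Ward scoring is given to the researcher, who has a stake in the result, and the sample size was planned with a one-tailed hypothesis. The nurses and the 5-minute rater are no better protected by the text.

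Randomization and concealed envelopes protect the comparison up to assignment. They do not protect it from scoring that differs by group afterwards, and no later analysis can remove that bias. Who scores the endpoint, and what that person may know, is a matter of trial conduct that this protocol itself settles. It is not something to leave to a statistical analysis plan.

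**Working it through.** **1. The plan's own figure.** Inputs from Material and Methods: 5% v 21%, one-tailed 5% level, 85% power, 62 per group. With pooled variance and no continuity correction, the mean rate is 0.13 and

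n = [1.645·√(2·0.13·0.87) + 1.036·√(0.05·0.95 + 0.21·0.79)]² / 0.16² ≈ 62.1 per group.

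This agrees with the stated 62 (63 if rounded up). Power at 62 is 0.849. The point does not dispute this figure.

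**2. Expected events.** 62 × 0.05 = 3.1 and 62 × 0.21 = 13.0, about 16 in all.

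**3. How few calls matter.** Assume no true effect and the same total, so 8 v 8 among 62 per group. Move k calls from positive to negative in one arm and k from negative to positive in the other. For k = 4 (4 v 12):

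- pooled rate = 16/124 = 0.129
- difference = 8/62 = 0.129
- standard error = √(0.129 × 0.871 × 2/62) = 0.0602
- chi-square = (0.129/0.0602)² = 4.59

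| Calls moved per arm | Events | Uncorrected chi-square p | Two-sided Fisher p |
|---|---|---|---|
| 0 | 8 v 8 | 1.00 | 1.00 |
| 2 | 6 v 10 | 0.28 | 0.42 |
| 3 | 5 v 11 | 0.108 | 0.179 |
| 4 | 4 v 12 | 0.032 | 0.058 |
| 5 | 3 v 13 | 0.007 | 0.014 |

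The protocol plans chi-square or Fisher's exact test. At 4 v 12 these fall on opposite sides of 5%. The continuity-corrected chi-square gives 0.061 and one-sided Fisher 0.029. With 65 per group the 4 v 12 chi-square p is 0.033.

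**4. A second illustration, through rater accuracy.** The Introduction quotes CAM sensitivity 86% and specificity 93%. Assume equal true incidence, 65 per group, one rating per patient, those values in one arm, and a shift to 80% and 96% in the other. The shift is an assumption; the protocol gives no such figure. Observed rate = p·sensitivity + (1 − p)·(1 − specificity).

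- True 5%: 0.05·0.86 + 0.95·0.07 = 0.1095, against 0.05·0.80 + 0.95·0.04 = 0.078.
- True 21%: 0.21·0.86 + 0.79·0.07 = 0.236, against 0.21·0.80 + 0.79·0.04 = 0.200.

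Exact binomial enumeration of the pooled z-test gives one-sided false-positive rates of 15% and 13% (two-sided about 10% and 8%). With equal accuracy in both arms the rate is about 5%. A larger assumed shift, to 70% and 98%, gives 32% and 28% one-sided.

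**5. Safeguards set against raters.** The envelope has a named opener, the coordinator. The nurses and the researcher are named as raters, and the 5-minute rater is not named. No sentence found links the two lists: none says that the coordinator keeps the group from the raters, that a rater stays out of the anaesthetic, or that the chart is withheld.

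**The case against.** The strongest reply is that the protocol documents no unblinding. The coordinator, not the researcher, opens the envelope, and nothing says that the researcher gives the anaesthetic, reads the chart or learns the group. That stands. A reader might infer that the researcher scores with knowledge of the group, but the text supports only that nothing prevents it. A reader might also infer that an anaesthetist scores the 5-minute reading. The text names no one.

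The second reply is that the ward readings may decide little. The Introduction cites a study of 400 patients with delirium signs in 31% on PACU admission and 4% at PACU discharge. If any positive reading counts, a ward rater cannot undo a PACU positive. This also stands, and no figure here isolates ward-only events. It is why the point covers every rater and not the researcher alone, since the nurses are not said to be unaware of the group either.

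The third reply is that the illustration needs eight calls moved in a coordinated way, and that three per arm would not reach 5%. That is correct. A reader might take the shift to lie within CAM's quoted error because 4 of 62 is only 6.5%, but that uses the wrong denominators. Losing 4 of 8 cases is 50% against a quoted miss rate of 14%, and gaining 4 of 54 non-cases is 7.4% against 7%. The shift is therefore not small by that standard. CAM's quoted error is also general instrument error, not error that differs by group.

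Finally, the documents fix no direction for the bias. The objective is non-directional, and the sample-size section does not say which group counts as exposed.

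**Conclusion.** The point holds as a missing safeguard affecting the trial's only outcome. In the text available, no rater of delirium is kept unaware of the group once the envelope is open. The front pages were not available, so a blinding term there cannot be excluded, but the Methods text that assigns the raters contains none.

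The size of any bias is unknown. With about 16 expected events the result is sensitive to a few borderline calls scored differently by group. Under the assumptions above, four moved calls per arm bring a null result to p = 0.032 or 0.058, depending on which planned test is used. These are illustrations of sensitivity and do not predict that bias will occur. They do not support a claim that the researcher is unblinded or that the result will be biased in a given direction. The change is worth making because it is cheap and the harm could not be repaired in the analysis.

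**What to change.** Add to Material and Methods:

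1. No one who scores CAM or RASS for a patient may have opened that patient's envelope, given or attended the anaesthetic, or seen the anaesthetic chart before scoring.
2. Allocation is withheld until database lock from the researcher who makes the ward ratings.
3. A rater meeting condition 1 is named for the 5-minute reading; otherwise that reading is analysed separately.
4. At each assessment the rater records whether the group was known.

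Simply moving ward scoring to the PACU nurses would not settle the matter, because the text gives them no protection either.

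**Cost.** No change to sample size and, on the face of the design, no new staff. Both arms receive a spinal injection and the same general anaesthetic, so withholding the group is largely feasible. There are two drawbacks. Residual leg block may reveal the group in the PACU, which item 4 would at least document. And the researcher could not give the anaesthetic to patients whom the researcher later rates.

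### The 85% power rests on a single-tailed test, but the objective and planned analysis name no direction; read two-sided, the power is below 85%

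*Protocol*

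**What the plan says.** All the relevant text is in the protocol.

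- **Objectives (section 3).** The aim is to learn whether the techniques "differed in relation to the incidence of postoperative delirium". No direction is given.
- **Material and Methods, sample-size list.** Delirium is taken as 5% in the exposed and 21% in the unexposed, with "Calculated relative risk: 0.2381", a 5% level, 85% power and "Hypothesis testing: single-tailed". The result is 62 per group, raised to 65 for losses. The list does not say which arm is the exposed one.
- **Material and Methods, analysis paragraph.** For the association with delirium, "the independence test (chi-square or Fisher's exact) will be applied", followed by simple and multiple logistic regression. Then: "In all tests, a significance level of 5% will be set". Neither sentence mentions a tail.

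**The concern.** A power figure belongs to one particular test. Here 85% belongs to a one-tailed test at 5%, while the question and the analysis are worded without direction. A chi-square test of independence at 5% rejects for a difference either way, and so in effect spends 2.5% on each side.

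Two things are at stake. First, a null result would be read against 85% power that the analysis, in its usual form, does not have. Second, the sample-size entry could later be cited to support a one-tailed claim at 5%, which doubles the conventional 2.5% error rate for a claim of benefit. The assumed rates imply about 3 events against 13 (62 × 0.05 = 3.1; 62 × 0.21 = 13.0). With so few events, a result that is significant under one reading and not under the other is a realistic outcome.

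**Working it through.** **Inputs** (Material and Methods): p1 = 0.05, p2 = 0.21, level 5%, power 85%, 62 per group calculated, 65 planned. The relative risk agrees: 0.05 / 0.21 = 0.2381.

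**Step 1: reproduce the protocol's figure.** The pooled-variance formula without continuity correction is

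n = [z_α √(2 p̄(1 − p̄)) + z_β √(p1(1 − p1) + p2(1 − p2))]² / (p2 − p1)²

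with p̄ = 0.13. Then √(2 × 0.13 × 0.87) = 0.4756, √(0.0475 + 0.1659) = 0.4620, (p2 − p1)² = 0.0256 and z_β = 1.036.

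- One-tailed, z_α = 1.645: n = (0.7823 + 0.4788)² / 0.0256 = 62.1. The protocol states 62.
- Two-sided, z_α = 1.960: n = (0.9322 + 0.4788)² / 0.0256 = 77.8, so 78.

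Other one-tailed formulas give 60 (unpooled), 58 (arcsine) and 75 (continuity-corrected). The two-sided continuity-corrected formula gives 90. The stated 62 is therefore a one-tailed result from the pooled formula, and it is correct as such.

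**Step 2: power by the same formula.** Power = Φ[(0.16 √n − z_α × 0.4756) / 0.4620].

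- One-tailed, n = 62: (1.2598 − 0.7823) / 0.4620 = 1.034, giving 84.9%.
- Two-sided, n = 62: (1.2598 − 0.9322) / 0.4620 = 0.709, giving 76.1%.
- Two-sided, n = 65: (1.2900 − 0.9322) / 0.4620 = 0.775, giving 78.1%.

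**Step 3: power of the tests the protocol names.** For each pair of event counts in the two arms, take the product of the two binomial probabilities, and sum over the pairs for which the test rejects at 5%.

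| Test | 62 per group | 65 per group |
| --- | --- | --- |
| One-tailed, formula (the sample-size basis) | 84.9% | 86.4% |
| Two-sided, formula | 76.1% | 78.1% |
| Two-sided uncorrected chi-square, exact | 78.7% | 80.7% |
| Two-sided chi-square, Fisher if an expected count is below 5, exact | 78.4% | 80.5% |
| Two-sided Fisher always, exact | 70.0% | 72.9% |
| One-tailed Fisher always, exact | 81.4% | 83.2% |

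The threshold of 5 in the fourth row is an assumption, since the protocol gives no rule for choosing between the two tests. At the assumed rates the expected delirium count is about 8 per arm ((3.1 + 13.0) / 2), so such a rule would seldom switch to Fisher.

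**The case against.** The best defence is that the only statement on sidedness in the protocol is the single-tailed entry, and that it stands under the opening words of the statistical paragraph. Fisher's test, a Wald test in logistic regression and the signed root of a 2 × 2 chi-square can all be run one-tailed. On that view the design is coherent and the analysis sentence is merely terse, and a separate analysis plan could say so.

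Part of this stands. A reader might infer that the protocol declares its tests two-sided; it does not. That reading comes from the non-directional objective and from the usual conduct of a test of independence. What the protocol does show is that the single tail appears only as a sample-size input and is carried into neither the objective nor the analysis. Sidedness, level, test and power are all fixed in this document, so the mismatch is the protocol's own.

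Three other strong readings also fail.

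- **That the calculation is wrong.** It reproduces.
- **That the trial has 70% power.** This holds only if Fisher's test is used whatever the counts.
- **That the direction is wholly open.** The two rates and the relative risk make exposure protective. Bupivacaine is the only difference between the arms and so the natural exposure. What is missing from the text at hand is the label itself. The sample-size paragraph also refers to an annex that is not in that text.

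It is also tempting to argue that harm from the added local anesthetic is likely, because the introduction mentions hypotension in one place and perfusion pressure in another. The protocol draws no such link, and the point does not need it.

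**Conclusion.** The point holds as an inconsistency between the basis of the sample size and the planned analysis. It is not an arithmetic slip. The 85% is the power of a one-tailed comparison that the objective and the analysis paragraph do not describe.

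Under the two-sided reading the shortfall depends on the test. It is about 7 to 9 points by the formula, about 4 to 6 points for the uncorrected chi-square by exact enumeration, and about 12 to 15 points if Fisher's test is always used. A one-tailed Fisher test also misses 85%, even with all 65 per group evaluable.

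These figures assume the protocol's own rates of 5% and 21%, equal groups, and between 62 and 65 evaluable patients in each. Keeping 85% two-sided by the formula would take 78 evaluable per group. The finding does not require that enlargement; it requires that the stated power match the stated test.

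**What to change.** In the sample-size list, replace the single-tailed entry with a two-sided 5% primary test of group by delirium, and name that test; the uncorrected chi-square is suitable. Restate the power for 62 to 65 evaluable per group as about 76% to 78% by normal approximation (79% to 81% exact). If Fisher's test is chosen instead, state 70% to 73%. Use the same test and sidedness in the analysis paragraph.

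If the sponsor prefers to keep a one-tailed test, the analysis paragraph must say so, state which arm is the exposed one and justify the direction. It should also note that a one-tailed Fisher test gives only 81% to 83%.

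Either route is a change of wording, best made before outcome data are seen, and adds no patients. The cost of the two-sided route is a less favourable stated power.

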**5 RESULTS**

Project in progress.

**6 DISCUSSION**

Project in progress.

**7 CONCLUSION**

Project in progress.

**SUPPLEMENT 1 – Confusion Assement Method - CAM**

**Confusion Assement Method - CAM**

**1. Acute onset**

There is evidence of acute change in the underlying mental state of the patient? (YES NO)

**2. Attention disorder**

Did the patient have difficulty focusing his attention, for example, easily distracted or had difficulty keeping up with what was being said? (YES) (NO)

**3. Disorganized Thinking**

Was the patient's thinking disorganized or inconsistent, with scattered or irrelevant conversion, unclear or illogical flow of ideas, or unpredictable change of subject? (YES) (NO)

**4. Change in level of consciousness**

Does the patient have altered level of consciousness such as lethargy, numb, comatose? (YES) (NO)

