Some disadvantages of this procedure associated with the Trendelenburg position would be pulmonary pathophysiological changes with the formation of atelectasis and increased airway pressure. They are also associated with increased intracranial pressure and the formation of cerebral edema. These effects could lead to low cerebral perfusion and potential mismatch of oxygen supply to the brain (CONACHER et al. 2004; CLOSHEN et al. 2014; ROSENDAL et al. 2014).

For laparoscopic surgeries, general anesthesia with short-term agents is almost unanimous. With regard to the technique for maintaining general anesthesia, there are currently two techniques: total intravenous anesthesia and inhalation anesthesia. Both are universally used, with rare exceptions for one technique to be more advantageous compared to the other technique, as in certain specific situations. Total intravenous anesthesia would be better indicated for patients with a history of nausea / vomiting in the postoperative period (APFEL et al. 2002; LEE et al. 2015), it is not a triggering agent of malignant hyperthermia (HOPKINS 2000; MANI and MORTON 2010) less disorders of behavior in the postoperative period of pediatric surgery (ORTIZ et al. 2014), anesthesia in neurosurgery with a tendency to intracranial hypertension (PETERSEN et al. 2003). Inhalation anesthesia would be more beneficial with neuroprotection (KITANO et al. 2007), cardioprotection (FRABDORF et al. 2009; PS 2010) and less chance of intraoperative recall (AMERICAN SOCIETY OF ANESTHESIOLOGISTS TASK FORCE ON INTRAOPERATIVE AWARENESS 2006).

The association with spinal anesthesia, provided that the guidelines for its contraindications are followed (TABLE 1), is also seen as advantageous, since it produces earlier awakening, reduces nausea and vomiting, postoperative pain, length of hospital stay, effective cost, improvement patient satisfaction (BESSA et al. 2012; CARD et al. 2015; DAY et al. 2015; GERGES et al. 2006; GHOSH et al. 2015; SINHA et al. 2009; WONGYINGSINN et al. 2012) and mainly the decrease consumption of anesthetic agents for general anesthesia (GERGES et al. 2006).

Chart 1 - Contraindications to spinal anesthesia.

| Absolute | Relative |
| --- | --- |
| Patient refusal | Coagulopathy |
| Significant hypovolemia | Sepsis / bacteremia |
| Infection at the puncture site | Previous neurological disease |
| Intracranial hypertension | Peripheral neuropathy |
| Significant coagulopathy | Multiple sclerosis |

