The Richmond Agitation Sedation Scale (RASS) scale, developed with the objective of characterizing the level of consciousness and agitation, is routinely used in association with CAM to characterize delirium. Signs of hyperactive delirium are defined with a RASS score ranging from +1 (anxious patient) to +4 (agitated patient) accompanied by positive CAM. Signs of hypoactive delirium will be defined as RASS ranging from - 5 (patient does not respond) to 0 (calm or sleepy patient) accompanied by negative CAM (NASSAR et al. 2008; SESSLER et al. 2002) (ANNEX 2).

Currently, the most accepted hypothesis for the pathophysiology of delirium in the postoperative period seems to be an acute neurological insult in a patient with a susceptible substrate. Such a disjunction results from an alteration in the balance of neurotransmitters or neuroinflammatory mediators in the brain, resulting in clinical symptoms of delirium. The most commonly affected pathways include acetylcholine, dopamine, gamma aminobutyric acid (GABA) and serotonin, where the most common neuroinflammatory marker involves the hypothalamic pituitary axis, represented by cortisol, as well as C-reactive protein (CRP), pro calcitonin, tumor necrosis and various interleukins such as IL-6, IL-8 and IL-10 (ALI et al. 2011). Although there is general acceptance of which clinical indicators define the susceptible substrate, there has been an increase in efforts to identify preoperative and postoperative biochemical markers that may help to identify potential risks for delirium based on the aforementioned theories (MCDANIEL and BRUNEY 2012) .

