**Criteria 1 and 2 plus 3 or 4 must be present.**

Adapted from: (INOUYE SK, VAN DICK CH, ALESSI CA 1990)

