**SUPPLEMENT 2 - Richmond Agitation Sedation Scale - RASS Richmond Agitation Sedation Scale - RASS**

| **Score** | **Term** | **Description** |
| --- | --- | --- |
| + 4 | Combative | Overtly combative or violent; immediate danger to staff |
| + 3 | Very agitation | Pulls on or removes tube(s) or catheter(s) or has aggressive behavior toward staff |
| + 2 | Agitated | Frequent nonpurposeful movement or patient–ventilator dyssynchrony |
| + 1 | Restless | Anxious or apprehensive but movements not aggressive or vigorous |
| 0 | Alert and calm |  |
| - 1 | Drowsy | Not fully alert, but has sustained (more than 10 seconds) awakening, with eye contact, to voice |
| - 2 | Light sedation | Briefly (less than 10 seconds) awakens with eye contact to voice |
| - 3 | Moderate sedation | Any movement (but no eye contact) to voice |
| - 4 | Deep sedation | No response to voice, but any movement to physical stimulation |
| - 5 | Unarousable | No response to voice or physical stimulation |

Source: Adapted from: (SESSLER et al. 2002).

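### No minimum level of arousal is set for a valid CAM, so a patient unresponsive from residual anaesthesia can be counted as delirious

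*Protocol*

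**What the plan says.** Delirium is the trial's stated outcome (protocol, Objectives; Material and Methods, statistical paragraphs). It is assessed with the CAM in combination with the RASS.

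- **Timing (Material and Methods).** The first assessment is set at "5 minutes after extubation, vital signs (blood pressure, heart rate, saturation) will be collected and the patient will be evaluated for delirium". Further assessments follow on arrival in the recovery room, every 30 minutes until discharge from it, and then every 24 hours.
- **CAM items (Supplement 1).** Item 1 asks whether "There is evidence of acute change in the underlying mental state of the patient". Item 2 is met by a patient who is "easily distracted or had difficulty keeping up with what was being said". Item 4 asks "Does the patient have altered level of consciousness such as lethargy, numb, comatose".
- **CAM rule (end of Supplement 1).** "Criteria 1 and 2 plus 3 or 4 must be present". The background gives the same rule.
- **RASS (Supplement 2).** At -4 there is no response to voice. At -5 there is "No response to voice or physical stimulation".
- **RASS range (introductory background, before section 2).** "Signs of hypoactive delirium will be defined as RASS ranging from - 5 (patient does not respond") up to 0. The sentence pairs this range with a negative CAM.

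No section states a minimum RASS for a valid CAM, provides a not-assessable category, or excludes residual drug effect from item 1.

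**The concern.** Items 2 and 3 ask about attention, following speech and the flow of conversation. None of these can be tested in someone who does not respond to voice. The form offers only YES or NO, and item 4 names coma as a YES. The first reading comes 5 minutes after extubation, following midazolam, fentanyl, propofol, rocuronium, remifentanil and desflurane. Unresponsiveness at that point may be no more than incomplete emergence.

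If such readings count, the outcome mixes delirium with slow emergence. False positives at the same rate in both groups dilute the contrast and cost power. At different rates they could produce a difference where there is none.

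**Working it through.** **1. Scoring a patient at RASS -4 or -5 with the form as written**

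| CAM item | What the form asks | Can it be marked YES? |
|---|---|---|
| 1 | Acute change in mental state | Yes: the patient was alert before anaesthesia, and drug effect is not excluded |
| 2 | Difficulty focusing or following speech | Yes: the patient does not follow speech |
| 3 | Disorganised thinking | Cannot be judged, and is not needed if item 4 is YES |
| 4 | Altered consciousness, coma included | Yes, by the form's own example |

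Items 1, 2 and 4 together satisfy the rule, so the reading can be CAM-positive. Item 4 alone would not be enough.

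**2. The plan's own figure**

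Inputs (Material and Methods): 5% vs 21%, one-sided 5%, power 85%, 62 per group calculated, 65 planned. The pooled formula uses the mean rate 0.13:

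n = [1.645·√(2·0.13·0.87) + 1.036·√(0.05·0.95 + 0.21·0.79)]² / 0.16² = 62.1

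This agrees with the stated 62 (63 if rounded up). One-sided power is 84.9% at 62 and 86.4% at 65 per group.

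**3. Equal false positives in both groups**

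The protocol gives no rate, so f is assumed. It is the share of truly non-delirious patients who become cases only through an unresponsive reading. I also assume that any positive reading makes a patient a case. Then

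observed rate = p + (1 − p)·f

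For f = 5%: 0.05 + 0.95·0.05 = 9.75% and 0.21 + 0.79·0.05 = 24.95%. Power is

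Φ{[Δ√n − 1.645·√(2·p̄·(1 − p̄))] / √[p₁(1 − p₁) + p₂(1 − p₂)]}

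with Δ = 0.152, p̄ = 0.1735 and n = 65, which gives 74.4%.

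| Assumed f, both groups | Observed rates | Relative risk | One-sided power, 65 per group | n per group for 85% |
|---|---|---|---|---|
| 0 | 5.0% vs 21.0% | 0.238 | 86.4% | 63 |
| 2% | 6.9% vs 22.6% | 0.306 | 81.6% | 73 |
| 5% | 9.75% vs 24.95% | 0.391 | 74.4% | 88 |
| 10% | 14.5% vs 28.9% | 0.502 | 63.8% | 117 |

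**4. Unequal false positives, no true difference**

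Here true delirium is 5% in both groups of 65, and every pair of counts is enumerated with its binomial probability. The one-tailed test is at a nominal 5%.

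| Assumed f in the two groups | Observed rates | Pearson test rejects |
|---|---|---|
| 0 vs 0 | 5.0% vs 5.0% | 6.0% |
| 2% vs 1% | 6.9% vs 5.95% | 8.6% |
| 5% vs 2% | 9.75% vs 6.9% | 14.9% |

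The protocol also allows Fisher's exact test, which rejects in 8.9% of trials in the 5% vs 2% case.

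**The case against.** **The misscoring is not certain.** Items 1 and 2 are needed as well as item 4, item 2 does not say how to mark a patient who cannot be tested, and the recovery-room nurses are trained beforehand. This stands. The form allows the error; it does not compel it.

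**A SAP or assessor manual could deal with it.** In part this is right: if RASS is stored beside each CAM, affected readings can be found later. But the protocol already fixes the form and its rule, and that form names coma as a positive feature. This is a stated rule, not an omitted detail.

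**The RASS range is background text.** It describes subtypes and is paired with a negative CAM, which contradicts the CAM rule in the same background and in Supplement 1. It is therefore weak support. The point rests on Supplement 1 and the timing, which suffice without it.

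**A cut at -4 is a choice.** At -3 there is movement but no eye contact to voice, so attention is hard to judge there too. This stands. The boundary at -4 is where Supplement 2 first records no response to voice; lighter sedation is not resolved by it.

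**A stronger reading is tempting: that the error falls more often on Group 1.** A reader might infer this because the background says of spinal anaesthesia that "it produces earlier awakening, reduces nausea and vomiting" and that it lowers general anaesthetic use, and only Group 2 receives local anaesthetic. The protocol does not support the step. That statement concerns spinal anaesthesia in general, and both groups receive a spinal injection. Both have the same induction and the same BIS target of 40 to 60. The reading is timed from extubation, so earlier awakening may bring extubation forward without changing arousal 5 minutes later. The sample-size text does not say which group is the exposed one.

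**The cited recovery-room cohort might seem to supply a rate.** It reports 31% with delirium on arrival, 56% of them with hypoactive signs (0.31 × 0.56 = 17.4% of patients). That does not measure RASS -4 or -5 and cannot be used for f.

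**Conclusion.** The point holds as a defect in how the trial's outcome is scored. With coma as a positive item, no arousal floor and a first reading 5 minutes after extubation, an unresponsive patient who is not delirious can be counted as a case.

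Its size is unknown. Under assumed equal false positives of 2% to 10%, one-sided power at 65 per group falls from 86.4% to between 81.6% and 63.8%. RASS -4 or -5 after extubation may be uncommon, so the upper end is a scenario, not an estimate. The figures also assume that one positive reading suffices and that f is net of patients who would be positive at another reading anyway.

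An imbalance between groups is possible but unproven. If it occurred, the type I error would rise by an amount that depends on the assumed rates and on the choice of test. The sample size of 62 is not in dispute on this point.

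**What to change.** - Score RASS first at every reading. At RASS -4 or -5, record the CAM as not assessable, neither positive nor negative, and use the next scheduled reading.
- Base the patient-level outcome on assessable readings.
- Report the number of not-assessable readings by group, with one sensitivity analysis that counts them as positive.
- Align the examples in item 4 of Supplement 1 and the RASS range in the background with this rule.
- Reconcile the background's negative CAM for hypoactive delirium with the CAM rule stated there and in Supplement 1. This is a separate contradiction; correcting it alone would leave the present gap open.

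The cost is a line on the CAM form, a line in the outcome definition and a corrected background sentence. RASS is already part of the assessment, and no visits or staff are added. A few early readings drop out, mostly replaced on arrival in the recovery room or 30 minutes later.
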